### 2.13 Quality oversight

To ensure protocol adherence and data integrity, a comprehensive quality oversight system was implemented:

(1) Monthly progress reviews will be conducted by the study management team to evaluate protocol adherence, recruitment progress, and data quality metrics; (2) An independent Data Monitoring Committee (DMC) comprising external statistician, clinician, and ethicist with no conflicts of interest will conduct biannual safety reviews and assess pre-defined stopping criteria; (3) Participant compliance will be tracked through returned moxa stick counts and treatment attendance, with deviations (> 20% missed sessions) escalated to the DMC; (4) Ethical oversight included institutional review board audits of adverse event reporting. All data modifications required dual approval (PI and DMC chair) post-audit, aligning with International Council for Harmonization-Good Clinical Practice Guideline (ICH-GCP) monitoring standards (23).

## 3 Discussion

Nocturia is a common age-related disease caused by multiple factors, rooted in circadian dysregulation of fluid homeostasis, which seriously affects the physical and mental health and quality of life in the elderly (24). HSM uses the medicinal power and heat of moxa fire to give the human body warm stimulation, stimulate human energy, and regulate the yin and yang balance of the internal organs through the conduction of meridian acupoints, ultimately achieving the purpose of harmonizing qi and blood and enhancing the body’s own resistance and defense. And further research indicated that the occurrence of heat-sensitive phenomenon is related to the plasticity changes of the brain neural network and the involvement of central glutamatergic neurons (25). While aging-related decline in AVP secretion is a well-established contributor, emerging evidence implicates ANP as a key mediator of nocturnal polyuria in non-cardiac populations. HSM may address this dual hormonal imbalance through its unique neuroendocrine modulation. The efficacy of HSM in preventing and treating diseases is much better than that of traditional moxibustion therapy. Compared with traditional moxibustion, HSM emphasizes the thermal moxibustion sensation and meridian qi transmission generated during the moxibustion process. By finding the thermal points for moxibustion to stimulate the meridian qi transmission, a small stimulus and a large response are produced to improve the efficacy (26). From a mechanism perspective, HSM may enhances therapeutic precision through three synergistic innovations. First, heat-sensitive points optimizes acupoint selection by dynamically targeting acupoint with aberrant thermal reactivity, a RCT focus on chronic fatigue syndrome showing that the total effective rate of the HSM group was 19.36% higher than that of the mild moxibustion group (93.55% vs 74.19%, *P* < 0.05) (27). Second, dose optimization is achieved by titrating moxa duration to individual “moxibustion sensation” thresholds, from warmth to radiation, and then propagation, ensuring adequate neurostimulation while avoiding thermal injury. Third, central plasticity modulation underpins HSM’s sustained effects: fMRI evidence reveals enhanced functional connectivity within the default mode network (DMN), particularly between the posterior cingulate cortex and hypothalamus (28), suggesting HSM may reset circadian rhythm centers by rewiring neural circuits governing AVP/ANP secretion. Together, these advances position HSM as a paradigm shift in precision moxibustion, bridging empirical practice with neurobiological validation. Recent studies have shown that HSM is more effective than mild moxibustion in reducing the frequency of nocturia, improving the degree of frequent urination, improving sleep quality and quality of life, and reducing the amount of residual urine in the bladder (28). However, there is a scarcity of clinical observational studies on the treatment of nocturia utilizing HSM, resulting in an insufficient amount of clinical data to substantiate its efficacy and safety.

This study aims to have a sample size of 110 patients, which will be one of the largest randomized controlled trials in this field. The target is to demonstrate the effect of HSM on nocturia in the elderly, clarify the amount of moxibustion, the distribution pattern of thermosensitive acupoints, the frequency of thermosensitive acupoints and the moxibustion sensation for the treatment of nocturia, and further clarify the regulatory effect of HSM on AVP and ANP, to provide experimental data for clarifying the therapeutic mechanism of HSM on nocturia in the elderly and direction for future basic research. Compared to previous studies (29, 30), our study boasts a shorter treatment duration, which is more readily acceptable to patients. Furthermore, our protocol places emphasis on the long-term maintenance effects of HSM, with reassessments of outcome measures conducted 2 months after treatment. Additionally, we aim to investigate the underlying regulatory mechanisms by analyzing and comparing changes in AVP and ANP levels before and after treatment. To ensure the integrity and scientific validity of the method, every step of the implementation of this clinical study will be strictly carried out, monitored and supervised.

Here are the limitations of our study: Firstly, the inclusion of only a limited number of patients as samples may restrict the representativeness and generalizability of our findings. Secondly, being a single-center study, our research may be influenced by the specific practices, patient demographics, or resource constraints of the institution, thereby limiting the broad applicability of our results. Lastly, with a follow-up period of just 2 months, our study may not adequately capture all significant clinical changes or adverse events associated with a chronic condition such as nocturia.

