**FIGURE 1 F1:**
[figure not shown]
The flow chart of the clinical procedures.

**TABLE 1 T1:** Schedule of enrollment, intervention and assessment.

Time point	Enrollment Week -1	Allocation Week 0	Treatment phase Week 1-2	Follow-up Week 3	Follow-up Week 10

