One treatment cycle consists of 5 days of treatment followed by 2 days of rest, with 2 consecutive treatment cycles being administered. To isolate the effects of the experimental intervention, all enrolled participants (both intervention and control groups) will be instructed to refrain from receiving any additional moxibustion treatments or traditional Chinese medicine therapies (e.g., acupuncture, cupping, herbal medicine) during the 8-week study period. These restrictions were communicated verbally and in written form at enrollment. And participants will be requested to complete weekly diaries to report any inadvertent use of prohibited therapies.

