### 2.8 Outcome measures

#### 2.8.1 Primary outcomes

The frequency of nocturia: 72-hour urination diary.

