### 2.12 Data collection and analysis

The data of various observation indicators of patients were collected on the day of treatment, the day after the end of treatment and 2 months after the end of treatment. To ensure the accuracy and completeness of the data, we will adopt a double-entry method. PASW Statistics 18.0 software was used to establish a database for case investigation data that met the inclusion criteria, and data review was performed after data entry was completed.

The statistical analysis of the PASW Statistics 18.0 data was performed, encompassing descriptive statistics for clinical baseline data. For continuous outcomes, group differences will be analyzed using Student’s *t*-tests if data are normally distributed; otherwise, the Mann-Whitney U test will be applied. For categorical variables, Chi-square tests or Fisher’s exact tests will be used as appropriate. Efficacy evaluations utilized both intention-to-treat (ITT) and per-protocol (PP) populations, while safety assessments were conducted on the safety analysis set. In the intention-to-treat analysis, missing data due to withdrawal or dropout will be handled using the last observation carried forward (LOCF) method. Participants who received prohibited therapies were retained in the trial per the ITT principle but flagged for sensitivity analysis. Their data were analyzed both within the full cohort and in a subgroup excluding protocol violators. When necessary, multiple imputation methods will be considered for missing value replacement, or alternative approaches will be selected based on actual circumstances. For clustering, the K-MEANS clustering method was utilized, while applying Pearson or Spearman correlation analysis to examine correlations. A *P*-value of 0.05 or less was considered statistically significant.

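### The protocol stresses long-term maintenance, but follow-up ends about 8 weeks after treatment and the stated tests name no estimate of how the arm difference changes from Week 3 to Week 10

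*Protocol article*

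**What the plan says.** All places are in the protocol article.

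- **Section 3, Discussion:** "our protocol places emphasis on the long-term maintenance effects of HSM, with reassessments of outcome measures conducted 2 months after treatment". The limitations paragraph of the same section says that "with a follow-up period of just 2 months, our study may not adequately capture all significant clinical changes or adverse events", and names nocturia as a chronic condition.
- **Section 2.5.2:** "One treatment cycle consists of 5 days of treatment followed by 2 days of rest, with 2 consecutive treatment cycles being administered", which makes two weeks of treatment.
- **Table 1:** nocturia frequency, the scales and both hormones are measured in both arms at allocation, at Week 3 and at "Follow-up Week 10". Section 2.12 gives the same timing: data are "collected on the day of treatment, the day after the end of treatment and 2 months after the end of treatment".
- **Section 2.8.1:** the primary outcome is "The frequency of nocturia: 72-hour urination diary". No time point is named there.
- **Section 2.12:** "For continuous outcomes, group differences will be analyzed using" t-tests, or the Mann-Whitney U test if the data are not normal. Missing values from withdrawal or dropout are filled by LOCF in the ITT analysis, with multiple imputation considered when necessary.
- **Section 2.3:** the hypotheses concern improvement in nocturia frequency, sleep, quality of life and TCM scores. Maintenance is not among them.

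**The concern.** Maintenance is a statement about two visits: the difference between arms just after treatment is still there, wholly or in part, at the later visit. A test of the arms at Week 10 shows whether some difference exists then. It does not show whether the Week 3 difference was kept, halved or lost, and setting two P-values side by side does not show it either.

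The article gives maintenance prominence and states an analysis, but that analysis names no quantity that answers the maintenance question. Two further features matter. The stated tests make no covariate use of the baseline that the trial collects. And LOCF would write the Week 3 value into Week 10 for anyone lost in between, which supplies maintenance by assumption.

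What is at stake is the conclusion. A claim could come to rest on which visits reach significance, and the word long-term would describe a period that the authors themselves call short.

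**Working it through.** **1. Length of follow-up.** Treatment fills Weeks 1 and 2 and the last visit is Week 10: 10 − 2 = 8 weeks. This agrees with the stated 2 months. Within the Discussion, the same interval supports an emphasis on long-term effects and is then listed as a limitation.

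**2. The plan's own sample size.** Section 2.9 gives Z = 1.96, P = 0.5, E = 10%:
- n = Z²P(1 − P)/E² = 1.96² × 0.25 / 0.10² = 96.04, so 96.
- 96 × 1.15 = 110.4, so 110, or 55 per arm.

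The figure reproduces. It is a precision size for a single proportion, so it was not set for any contrast between visits.

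**3. Inputs for the rest.** From the document: 55 per arm and at most 15% dropout, so 55 × 0.85 = 46.75, about 47 per arm. The document gives no effect size, SD or between-visit correlation. *Assumed:* Week 3 arm difference d = 0.5 to 0.7 SD, correlation ρ = 0.5 to 0.7, equal SD at both visits.

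**4. Precision of the maintenance contrast.** For the change in arm difference from Week 3 to Week 10, in SD units, SE = √[(2/n) × 2(1 − ρ)] and the half-width is 1.96 × SE.

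| n per arm | ρ | 95% CI half-width (SD) |
|---|---|---|
| 47 | 0.5 | 0.40 |
| 47 | 0.7 | 0.31 |
| 55 | 0.5 | 0.37 |
| 55 | 0.7 | 0.29 |

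Losing half of d = 0.5 to 0.7 is a change of 0.25 to 0.35 SD, about the size of the half-width. Under a normal approximation, a 5% test of this contrast would miss such a loss in about 34% (n = 55, d = 0.7, ρ = 0.7) to 77% (n = 47, d = 0.5, ρ = 0.5) of trials.

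**5. What paired P-values would show.** The two visit z-statistics are taken as bivariate normal with means d√(n/2) and correlation ρ. Among trials with a significant Week 3 result:
- half the effect lost: Week 10 is still significant in 30% to 47%, which would read as maintained;
- nothing lost: Week 10 is not significant in 3% to 22%, which would read as lost.

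**6. LOCF.** Suppose 15% in each arm miss Week 10, their Week 3 value is carried forward, and their Week 3 effect is like that of the others. Then apparent retention = 0.85R + 0.15, where R is the true retained fraction:

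| True R | Apparent R |
|---|---|
| 0 | 0.15 |
| 0.25 | 0.36 |
| 0.50 | 0.58 |
| 0.75 | 0.79 |

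**The case against.** A reader might infer that the trial *cannot* estimate how much of the effect is kept. The documents do not support that. Table 1 measures both arms at baseline, Week 3 and Week 10, so the contrast can be computed. The weakness lies in the stated analysis and in precision, not in the visit schedule.

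A reader might also infer that the tests are to be run visit by visit. Section 2.12 speaks only of group differences and names no visit and no form of the variable. A t-test on the change from Week 3 to Week 10 would fit its words. Nor does any passage say that maintenance will be judged from paired P-values, so step 5 shows a risk and not a stated plan.

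Other points on that side also stand. A longitudinal model may be left to an analysis plan that is not shown, so its absence alone would be no finding. The arm difference at Week 10 is a valid estimate of the effect present at 2 months. The 2-month interval stands in the same sentence as the claim, and the short follow-up is disclosed, so the wording conflict alone is editorial. The proposed contrast will have a wide interval.

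These points narrow the concern but do not remove it. The article does fix an analysis, it fixes LOCF, and it puts weight on maintenance; the three do not fit together. A wide interval is no reason to leave the contrast out, since it shows how little the data can say about retention.

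**Conclusion.** The point holds in a limited form. Long-term is not supported by a last visit about 8 weeks after treatment, and it sits badly beside the authors' own limitation. The stated tests do not adjust for baseline and name no estimate of the change in arm difference from Week 3 to Week 10, although the planned data allow one.

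That estimate would be rough, with a 95% CI half-width of about 0.29 to 0.40 SD, and it may not detect loss of half the effect. The width rests on 47 to 55 analysed per arm and an assumed correlation of 0.5 to 0.7. The significance-pattern and missed-loss figures also rest on an assumed Week 3 effect of 0.5 to 0.7 SD. None of the assumed correlations or effect sizes is in the document, so the figures are illustrations.

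The change is worth making because it is cheap and alters what the trial can conclude about maintenance.

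**What to change.** 1. Analyse Weeks 3 and 10 in one mixed model adjusted for baseline, with arm, visit and arm-by-visit terms.
2. Report the arm difference at each visit, and its change from Week 3 to Week 10, each with a 95% CI. Base any maintenance statement on that change and not on separate P-values.
3. Do not fill missing Week 10 values by LOCF for this contrast. The mixed model can use the available Week 3 data under a missing-at-random assumption, which should be stated.
4. Describe the result as the effect 2 months after treatment and drop long-term.

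The cost is wording and one model on data already planned, with no new visits or patients. The downside is a more modest maintenance claim and a contrast with a wide interval. Baseline adjustment mainly helps the arm difference at each visit and should not be expected to narrow the contrast much.
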